#### Intervention group: unilateral hernia repair with contralateral exploration

Surgical inguinal hernia repair is done similarly in all patients. An incision is made in the groin. The hernia sac is identified, divided from the vas deferens and testicular vessels (in boys) and cleaned to the level of the internal inguinal ring. It is twisted on itself and ligated at the level of the internal inguinal ring. The skin is closed. Duration of unilateral inguinal hernia repair is approximately 60 min (including anaesthesia time). Exploration of the contralateral side and potential contralateral hernia repair will increase anaesthesia time by approximately 15 min.

Contralateral exploration will be used to identify a PPV or hernia on the other side than the side on which the child has to be operated on. If during contralateral exploration, a hernia or PPV is present, contralateral repair will be performed. This will be exactly the same procedure as the inguinal hernia repair on the symptomatic side. If a hernia or PPV is absent during contralateral exploration, the skin will be closed. There is no need for extension of postoperative hospital admission or addition of other interventions.

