### Explanation for the choice of comparators {6b}

#### Control group: unilateral hernia repair without contralateral exploration

In participants who are allocated to the control group, only unilateral hernia repair (without contralateral exploration) will be performed.

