#### Complications of anaesthesia and surgery

Complications related to inguinal hernia within 1 year after primary repair are as follows: wound infection, hematoma, hydrocele, testicular atrophy, apnoea or inguinal hernia recurrence. Apnoea, wound infection, hematoma and hydrocele will be assessed during hospital admission via monitoring (if applicable) and by the (fellow) paediatric surgeon. After hospital discharge, these complications will be assessed through a phone call performed by one of the investigators 4 weeks following surgery. Testicular atrophy and inguinal hernia recurrence will be assessed at the outpatient clinic 1 year following surgery. If there is partial or complete testicular atrophy of one testis (i.e. one of the testes is smaller compared to the other at follow-up), additional ultrasonography of both testes will be performed. Complications are defined as:
Testicular atrophy: No palpable testicular tissue in scrotum (=complete testicular atrophy) or testis documented to be smaller at follow-up than at time of inguinal hernia repair (=partial testicular atrophy) at operated side(s).Wound infection/surgical site infection: Infection occurring within 30 days of surgery; infection involving only the skin and subcutaneous tissue; at least one of the following: (a) purulent discharge from a superficial infection or (b) organisms isolated from aseptically obtained wound culture; and at least one of the following signs of infection: (a) pain or tenderness, (b) localised swelling and (c) redness or hyperthermia [24].Apnoea: Apnoea of infancy is defined as “an unexplained episode of cessation of breathing for 20 seconds or longer, or a shorter respiratory pause associated with bradycardia, cyanosis, pallor, and/or marked hypotonia requiring intervention”. Types of interventions recorded will include stimulation, assisted ventilation, continuous positive airway pressure (CPAP), endo-tracheal intubation and administration of methylxanthine [25].Recurrence: the hernia returns at the previously operated side and a reoperation on the same side is warranted.

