## Data collection and management

### Plans for assessment and collection of outcomes {18a}

Data of participants and findings for primary and secondary outcome measures will be recorded by the (fellow) paediatric surgeon or one of the investigators in a web-based electronic case record form using Castor EDC [30]. Parents/caretakers will use the online KLIK PROM (patient-reported outcome measures) portal (www.hetklikt.nu) to answer questionnaires.

The study will collect the following baseline characteristics and data from the participants: sex, gestational age, birth weight, comorbidities, inguinal hernia in first degree siblings, age and weight at day of surgery, preoperative size of both testes (in boys), side of the inguinal hernia and other hernia characteristics (e.g. preoperative history of hernia incarceration and surgical findings during contralateral exploration (i.e. presence of a PPV or not), total duration of surgery and hospital admission, total number of hospital visits and complications.

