#### Secondary study parameters

Secondary outcomes include the length of hospital stay and duration of operations (including anaesthesia time), complications of surgery and the health-related quality of life (HRQOL) of the operated infants and parental distress and anxiety. Mean (standard deviation, SD) or median (interquartile range, IQR) differences and corresponding 95% CIs will be calculated for length of hospital stay and duration of operations (including anaesthesia time). Odds ratio together with the 95% CI will be calculated for complications. Linear and logistic regression analysis will be performed to adjust for centre and possible confounders (sex, gestational age at birth and initial hernia side). Differences in HRQOL and parental distress and anxiety at baseline before surgery, 4 weeks and 1 year after primary hernia repair and, if relevant, prior to and 4 weeks after re-operation for MCIH will be reported using median and interquartile ranges.

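### Testicular atrophy is scored only at operated sides with no margin for measurement error, which tilts this secondary safety comparison against exploration by an amount the protocol does not let us fix

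*Protocol article*

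**What the plan says.** All references are to the protocol article.

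- **Definition.** Complications of anaesthesia and surgery defines complete atrophy as no testicular tissue palpable in the scrotum, and partial atrophy as a "testis documented to be smaller at follow-up than at time of inguinal hernia repair (=partial testicular atrophy) at operated side(s". No minimum change is given.
- **A second wording.** The same section describes partial or complete atrophy as the case where "one of the testes is smaller compared to the other at follow-up", after which "additional ultrasonography of both testes will be performed". It does not say how the scan affects the score.
- **Sides opened.** For controls, "only unilateral hernia repair (without contralateral exploration) will be performed". In the exploration arm both groins are opened: "If during contralateral exploration, a hernia or PPV is present, contralateral repair will be performed", and "If a hernia or PPV is absent during contralateral exploration, the skin will be closed". Whether a side explored and found negative is an operated side is not stated.
- **Baseline data.** Plans for assessment and collection of outcomes {18a} lists "preoperative size of both testes (in boys" among the items recorded, in both arms.
- **Analysis.** Under Secondary study parameters, "Odds ratio together with the 95% CI will be calculated for complications". The number of sides scored per child is not mentioned.

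**The concern.** Any rule that calls every recorded decrease atrophy will produce some false positives per testis examined. If the arms differ in how many testes are scored, they differ in how many false positives they can collect. An explored boy contributes two testes and a control boy, at primary surgery, one. The same chance reading on the contralateral side is a complication in the first boy and nothing in the second.

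The second wording has the same asymmetry. If one testis simply happens to be the smaller, it always lies on an operated side when both sides count as operated. In a control boy operated on one side it does so about half the time.

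Background and rationale {6a} names testicular atrophy among the risks of exploration and mentions infertility if both testes are affected. The Objectives section hypothesises that surgical risk equals that of symptomatic repair. A comparison biased by its counting rule would bear on that hypothesis. For children in general the background section gives an atrophy rate of 0–0.3%, so a false-positive rate of even 1% per testis would exceed it.

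**Working it through.** **The plan's own figure.** The article gives no figure for atrophy. The 378 belongs to the primary outcome: 10% against 2.5%, two-sided alpha 0.05 and power 0.80, with a continuity correction, gives 189 per arm, or 378. It reproduces and is not affected here.

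**Inputs from the article.** One side is opened in controls and two in the exploration arm. About 10% of children are expected to be reoperated for MCIH (Sample size {14}); I apply this to control boys, as r = 0.10.

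**Inputs assumed.** These are not in the article:
- false-positive probability m per scored testis: 2%, 5% and 10%
- correlation ρ between a boy's two testes: 0 or 0.5
- share q of explored sides that are repaired: 30% to 70%
- boys per arm: 150

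**Formulas, with no true atrophy in either arm.**
- One testis scored: m.
- Either of two testes: B = 1 − [(1 − m)² + ρm(1 − m)].
- Controls with reoperations: (1 − r)m + rB.
- Exploration arm if only repaired sides count: (1 − q)m + qB.

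**Worked at m = 5%.**
- A, simplest case: B = 1 − 0.95² = 0.0975 against 0.05. OR = (0.0975/0.9025)/(0.05/0.95) = 2.05.
- B, adding control reoperations: control = 0.9 × 0.05 + 0.1 × 0.0975 = 0.0548. OR = 1.87.
- C, adding ρ = 0.5: B = 1 − (0.9025 + 0.5 × 0.0475) = 0.0737; control = 0.045 + 0.0074 = 0.0524. OR = 1.44.
- D, as B but only repaired sides count, q = 0.5: exploration = 0.025 + 0.0488 = 0.0738 against 0.0548. OR = 1.37.

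| Scenario | OR at m = 2% | 5% | 10% |
|---|---|---|---|
| A: two testes v one, independent | 2.02 | 2.05 | 2.11 |
| B: A + 10% control reoperations | 1.84 | 1.87 | 1.92 |
| C: B + correlation 0.5 | 1.43 | 1.44 | 1.45 |
| D: B, repaired sides only, q = 30% | 1.18 | 1.19 | 1.19 |
| D: q = 50% | 1.37 | 1.37 | 1.39 |
| D: q = 70% | 1.55 | 1.57 | 1.59 |

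**Chance of a significant result with no true harm** (150 boys per arm, Fisher's exact test, summed over the two binomial distributions), at m = 2%, 5% and 10%:
- A: about 9%, 27% and 54%
- C: about 3%, 7% and 15%
- D with q = 50%: about 2%, 6% and 12%

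A normal approximation gives 17%, 35% and 61% for A. It is not reliable at the low end, where only 150 × 0.02 = 3 and 150 × 0.0396 = 5.9 events are expected.

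**With the same testes scored in both arms**, the false-positive probability is equal by construction and the spurious odds ratio is 1.0, apart from any assessor bias.

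**The case against.** Restricting atrophy to operated sides is a conventional way to attribute it to surgery. Exploration does expose a second testis, and true atrophy there is a genuine cost of the strategy. Scoring untouched testes adds background noise to both arms and can dilute a real signal. All of this stands. It limits the criticism to false positives and identifies the price of the remedy, but it does not remove the asymmetry.

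Several stronger readings are tempting, and the article does not support them:
- **A doubling of the odds in all circumstances.** This needs independent errors, no control reoperations and every negative exploration counted as operated. The article expects about 10% reoperations and leaves the last point open; it is silent on correlation, which the same visit and examiner would make plausible.
- **The ultrasound plays no part in classification.** The article is silent on this. The full protocol may settle it, and the scan covers both testes in either arm.
- **The control arm's contralateral information is lost.** The preoperative size of both testes is recorded, so the comparison remains possible.
- **Testes outside the scrotum will often pass as complete atrophy.** Non-descended testis is an exclusion criterion, so only later displacement or ascent could do this.
- **Noise dominates throughout.** The 0–0.3% rate is for children generally. For preterm babies the background section gives 2 to 30%.

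Testicular growth over the year may also keep m low under the smaller-than-at-repair wording. Finally, the article does not say whether each complication gets its own odds ratio; in a composite the effect would be diluted.

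**Conclusion.** The point holds in direction, with a modest and uncertain size. The stated rule gives exploration boys more opportunities for a false positive than control boys, and nothing else in the article removes this. In every scenario examined the bias runs against exploration and the spurious odds ratio stays above 1: from about 1.2 to 1.6 if only repaired sides count, through about 1.4 and 1.8 to 1.9, to about 2.0 to 2.1 at most. The corresponding chance of a significant result without true harm runs from about 2% to 54% across the scenarios tested. The upper end needs a 10% error rate per testis, which no section supports.

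The error rate, number of boys, correlation and status of a negatively explored side are all assumptions. The matter concerns one secondary safety outcome; the primary outcome and its sample size are unaffected. The definition should be changed before analysis because the correction is cheap.

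**What to change.** 1. Score both testes in every boy in both arms, each against its own preoperative size. Compare the randomised arms on atrophy of either testis. This still captures true harm on a second operated side.
2. Show the contralateral testis separately by arm. The untouched side in controls then gives the background rate. Keep the operated-side count as a descriptive supplement, and state whether a negatively explored side belongs in it.
3. Reconcile the two wordings of atrophy (smaller than at repair; smaller than the other testis).
4. Set in advance a margin beyond measurement error, and state how the ultrasound already ordered enters the classification.

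The cost is a change of definition and one extra table. The baseline sizes, the 1-year assessment and the ultrasound are already planned. The downside is some added background noise and a slightly higher reported atrophy rate in the control arm.

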### Adverse event reporting and harms {22}

All adverse events reported spontaneously by parents of the subject or observed by the investigator or his staff will be recorded from the start of the study until the moment of first follow-up. If a life-threatening SAE likely related to the study is encountered, this SAE will immediately be reported to the Central Committee on Research Involving Human Subjects (CCMO) according to the CCMO guidelines, and the study will be paused instantly, if appropriate. Inguinal hernia repair is usually at most accompanied by minimal complications.

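### The only infection item among the complications is labelled surgical site infection but admits superficial infection alone, so a deeper groin infection is left out of the complication odds ratio

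*Protocol article*

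**What the plan says.** The section *Complications of anaesthesia and surgery* lists the complications that make up this secondary outcome: "wound infection, hematoma, hydrocele, testicular atrophy, apnoea or inguinal hernia recurrence". The list is introduced as the full set, with no residual category.

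Four of the six items are then defined. The infection item opens "Wound infection/surgical site infection: Infection occurring within 30 days of surgery" and adds a depth requirement: "infection involving only the skin and subcutaneous tissue". It next asks for one of two findings, either "purulent discharge from a superficial infection" or a positive wound culture, together with at least one local sign.

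The *Intervention group* section describes the repair: the sac is "divided from the vas deferens and testicular vessels (in boys) and cleaned to the level of the internal inguinal ring". If exploration shows a hernia or a patent processus vaginalis (PPV), the second side is repaired too: "This will be exactly the same procedure as the inguinal hernia repair on the symptomatic side". If it shows neither, the skin is closed.

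*Secondary study parameters* plans an odds ratio with a 95% confidence interval for complications. Separately, *Adverse event reporting and harms* says that all adverse events "will be recorded from the start of the study until the moment of first follow-up", and the data monitoring section gives an independent safety committee the task of monitoring complications.

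**The concern.** The label promises surgical site infection in general, while the definition delivers only its superficial form. The repair reaches well below the layer that the definition admits, so a deeper infection is a conceivable result of this operation. Such an infection fails the depth clause, and the outcome would then score the more serious event as no complication and the milder one as a complication.

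Harm is half of this trial's question. The *Objectives* section hypothesises that exploration carries the same surgical complication rate as repair of a symptomatic hernia. If the trial reports no excess of complications, readers will want to know that the worst wound infections were in the count.

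**Working it through.** **Does any listed item catch a deep infection?** The depth clause stands beside the time window and the clinical criteria as a separate requirement, so all must be met. A positive culture satisfies one of the two alternative findings, but it does not waive the depth clause. An infection extending below the subcutaneous layer therefore fails, whatever pus, culture or local signs are present. The other five items are bleeding, fluid collection, testicular loss, breathing events and return of the hernia; none is an infection item. No other section of the article supplies a deep category.

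**Where would the event appear?** It would be in the adverse event record and before the safety committee, but not in the complication odds ratio. Adverse event recording runs to first follow-up, and the first planned contact after discharge is at 4 weeks. That is 28 days against the definition's 30-day window.

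**Denominator.** The stated sample size reproduces. For 10% against 2.5%, two-sided alpha 0.05 and power 0.80, the two-proportion formula gives 163 per arm without continuity correction (326 in total) and 189 per arm with it. 2 × 189 = 378, as stated.

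**Expected wound infections.** *Background and rationale* gives 0.6–1.2% of children.

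- All infants: 378 × 0.006 = 2.3; 378 × 0.012 = 4.5.
- Each arm at that same rate: 189 × 0.006 = 1.1; 189 × 0.012 = 2.3.

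**Expected cases missed.** The documents give no share of infections that are deep. A range of 5–30% is an assumption.

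- Lowest: 378 × 0.006 × 0.05 = 0.11.
- Highest: 378 × 0.012 × 0.30 = 1.36.

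So about 0.1–1.4 infants in the whole trial would have an infection that the outcome does not count.

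**Can the difference between arms be sized?** No. The number of full second dissections in the exploration arm equals the number of infants found to have a contralateral PPV or hernia, and the article gives no rate for that finding.

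**The case against.** Three objections carry weight.

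First, harm data are not lost. A deep infection is an adverse event, the safety committee sees it, and a resulting readmission or hernia-related reoperation would show in length of stay, costs or the primary outcome. This stands. The gap is confined to the secondary complication outcome, though that is where the arms are formally compared on complications.

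Second, this is a condensed article. The full protocol (v1.8) is not shown, and two of the six complications are left undefined here, so the full document or the case report form may hold a deep category. That is possible. However, the infection definition is printed in full and restricts itself explicitly. This is a rule that is stated, not a detail that is left out. If the full protocol does differ, the two need to be aligned.

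Third, the numbers are too small to move an odds ratio materially. This also stands, and it sets the weight of the point.

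A reader might go further and infer that exploration doubles the deep dissections, so that the definition hides about twice as much harm in that arm. Using the infection rate per groin, that would give 378 × 0.006 to 378 × 0.012 = 2.3–4.5 infections in 189 explored infants against 1.1–2.3 in 189 controls. The documents do not support this. The rate is stated per child, not per groin. The full procedure is repeated only when a PPV or hernia is found, so doubling is an upper bound. The *Objectives* section also expects fewer complications after a negative exploration.

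**Conclusion.** The point holds as a mismatch between label and definition. As written, the infection item counts superficial infection only, no other listed complication covers a deeper one, and such an event stays out of the complication odds ratio while remaining visible in the safety records.

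It is minor. About 0.1–1.4 cases would be missed in 378 infants, resting on the article's per-child rate and an assumed deep share of 5–30%. With only 2.3–4.5 wound infections expected in total, a single missed case would be noticeable in the tabulation but would not change the trial's conclusion. The definition does not bear on the primary outcome, which depends on reoperation. More operating on the second side makes an uneven omission plausible, but neither a bias in favour of exploration nor its size can be shown from the documents.

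**What to change.** Replace the depth clause with *infection at the operated site at any depth*, take the word *superficial* out of the purulence criterion, and record depth (superficial or deep) as a sub-category. Deleting *only* is not enough by itself: the clause would still require involvement of the skin and the layer beneath it, and the purulence criterion would still be superficial.

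The article reports 302 infants included by 24 August 2021. For infants already enrolled, apply the new definition from the adverse event record, using an assessor blinded to allocation; the blinding section already provides for blinded outcome assessors. Infections arising after adverse event recording stops may not be recoverable this way.

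The cost is one reworded definition and one field in the electronic case report form, with no extra visit or procedure. The drawback is that a secondary outcome definition changes during an open-label trial. Report it as such, and give the superficial-only count under the present definition beside the new one so that readers can see both.

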Surgeons may prefer performing contralateral exploration because of high MCIH incidence, high incarceration rate and repeated anaesthesia, carrying risk for near critical incidents (apnoea risk up to 12%) [12]. The US Food and Drug Administration (FDA) recently released an official warning regarding the potentially harmful impact of repeated general anaesthesia on the child’s brain [13]. Indeed, previous studies have shown that multiple exposures to general anaesthesia before 3 years of age is associated with neurocognitive and developmental problems (e.g. learning disabilities) [14–17]. More recent research has shown that the potential impact of a single session of general anaesthesia for hernia repair on functional brain development is not detectable [18, 19]. Yet, the effect of repeated anaesthesia on brain development remains unclear [13, 18]. These findings highlight the importance of preventing repeated surgery and anaesthesia. Contralateral exploration may help to reduce the frequency and total length of anaesthesia in children that develop MCIH after unilateral hernia repair.

Nonetheless, contralateral exploration also carries additional risks of operative complications: wound infection occurs in 0.6–1.2% of the children, hematoma in 0.1%, testicular atrophy in 0–0.3% and ipsilateral recurrence in 0.4–1.2% [20, 21]. In preterm babies, these risks are even higher: the recurrence rate varies from 2 to 8.6% and the risk of testicular atrophy, which may be accompanied by loss of function, ranges from 2 to 30% [3, 5]. If both testes are affected, boys may become infertile. As not all PPVs necessarily become hernias, contralateral exploration and its additional risks will be unnecessary in some children [22]. Consequently, the debate continues whether or not to perform contralateral inguinal exploration in infants with inguinal hernia [4, 9, 20]. Cost-effectiveness of both strategies in children has never been assessed.

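### Apnoea, the only anaesthesia-type complication listed, must be *unexplained* to count, so an episode of 20 seconds or longer put down to the anaesthetic can fall outside the endpoint

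*Protocol article*

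**What the plan says.** In the protocol article, under Complications of anaesthesia and surgery, the list reads: "Complications related to inguinal hernia within 1 year after primary repair are as follows: wound infection, hematoma, hydrocele, testicular atrophy, apnoea or inguinal hernia recurrence". The definition of the fifth item opens "Apnoea: Apnoea of infancy is defined as" and continues "an unexplained episode of cessation of breathing for 20 seconds or longer, or a shorter respiratory pause" accompanied by bradycardia, cyanosis, pallor or marked hypotonia, followed by a condition that intervention was needed. The interventions to be recorded range from stimulation to intubation and methylxanthine.

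On assessment, the section states: "Apnoea, wound infection, hematoma and hydrocele will be assessed during hospital admission via monitoring (if applicable) and by the (fellow) paediatric surgeon". It adds: "After hospital discharge, these complications will be assessed through a phone call performed by one of the investigators 4 weeks following surgery". Post intervention assessment extends outcome assessment to the period during, and 4 weeks after, repair of a metachronous contralateral hernia.

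Background and rationale {6a} presents apnoea as a hazard of repeated anaesthesia, "carrying risk for near critical incidents (apnoea risk up to 12" per cent). Secondary study parameters plans an odds ratio with 95% confidence interval for complications, with regression adjustment for centre and other factors. Concealment mechanism {16b} says that participants and care providers know the allocation.

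**The concern.** The trial's argument is partly about anaesthesia. Exploration adds about 15 minutes to the first anaesthetic and is hoped to spare some infants a second one. Apnoea is the listed complication that speaks to this trade-off. Yet the definition taken over for it belongs to a different condition, in which the absence of a cause is part of the diagnosis. A complication of anaesthesia is by its nature an event with a suspected cause.

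Two things are at stake. First, episodes that the outcome was set up to count may be scored as not meeting it. Second, whether an episode is explained is a matter of opinion. In hospital that opinion is given by the surgeon, who knows whether the infant had the longer anaesthetic. A criterion of duration and signs leaves less room for that knowledge to enter the score.

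**Working it through.** No figure in the plan rests on the apnoea definition, so the main check is a reading of the text. Arithmetic only bounds the possible effect.

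**Step 1: the sample size does not depend on this point.** Inputs from Sample size {14} and Sequence generation {16a}: 10% versus 2.5%, two-sided alpha 0.05, power 0.80, 1:1. The two-proportion formula gives n' = [1.96 × √(2 × 0.0625 × 0.9375) + 0.842 × √(0.10 × 0.90 + 0.025 × 0.975)]² / 0.075² ≈ 162.3, so 163 per arm. With the continuity correction, n = (n'/4) × [1 + √(1 + 4/(n' × 0.075))]² ≈ 188.1, so 189 per arm and 378 in total. This matches the plan, and apnoea enters nowhere.

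**Step 2: the definition against its use.**

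| Element | What the section gives |
|---|---|
| Purpose | Complications of anaesthesia and surgery |
| Anaesthesia-type items | Apnoea only, out of six |
| Limb 1 | Unexplained cessation of breathing, 20 seconds or longer |
| Limb 2 | Shorter pause with bradycardia, cyanosis, pallor or marked hypotonia |
| When assessed | Admission, then a call at 4 weeks |
| Who scores in hospital | The surgeon, with monitoring where it applies |

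Limb 1 carries *unexplained* beyond doubt. An infant who stops breathing for 20 seconds or longer in recovery, and whose surgeon blames the anaesthetic, therefore fails limb 1 as worded. Limb 2 need not carry the word, because the adjective stands with the first noun.

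**Step 3: how many events could be involved.** Per arm, 189 × 12% = 22.7 at the article's upper rate, and 189 × 6% = 11.3 at half that rate (an assumption).

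**Step 4: illustration of loss and dilution.** All rates here are assumptions. Let true anaesthesia-attributed apnoea be 12% in one arm and 6% in the other. Let *s* be the share not counted because it is explained, and *b* a background rate of other apnoea counted in both arms. The observed rate is q = p(1 − s) + b, and the odds ratio is [q₁/(1 − q₁)] / [q₀/(1 − q₀)].

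| s | b | q₀ | q₁ | Odds ratio | Power, 189 per arm |
|---|---|---|---|---|---|
| 0 | 0 | 12% | 6% | 0.47 | 0.53 |
| 0.5 | 0 | 6% | 3% | 0.48 | 0.29 |
| 0.5 | 2% | 8% | 5% | 0.61 | 0.22 |
| 0.75 | 5% | 8% | 6.5% | 0.80 | 0.08 |
| 1 | 2% | 2% | 2% | 1.00 | – |

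Losing the same share in both arms barely moves the odds ratio but costs precision. Dilution towards 1 also needs background events. The 12% versus 6% contrast is not a forecast. At the plan's reoperation rates, second anaesthetics number about 189 × 10% = 18.9 and 189 × 2.5% = 4.7. At 12% apnoea each, they add only about 2.3 and 0.6 events.

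**The case against.** The strongest reply is that the section, read as a whole, plainly means to capture perioperative apnoea. It provides for monitoring during admission and records interventions that belong to a recovery room or ward. Limb 2 can take in a shorter post-anaesthetic pause with cyanosis or bradycardia even on a literal reading. Adverse events observed by staff are recorded up to first follow-up, and a safety committee monitors all complications, so an explained apnoea need not vanish from the trial. Randomisation is stratified by centre and the analysis adjusts for centre, so a reading that is uniform within a centre affects both arms alike. Nothing shows that any site has applied the word literally.

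Most of this stands, and it rules out several stronger readings that a reader might infer:

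- *The apnoea count falls to zero.* This does not follow, because of limb 2 and the evident intent.
- *There is no time window and unrelated episodes count.* The section restricts the list to related complications within 1 year and sets two assessment times. What the definition lacks is a limit counted from anaesthesia, such as wound infection has ("Infection occurring within 30 days of surgery").
- *The arms cannot be compared.* Centre-level differences in reading cost events; they do not by themselves create a difference between arms.
- *Apnoea is the only complication frequent enough to compare.* Background and rationale {6a} gives preterm rates of 2–8.6% for recurrence and 2–30% for testicular atrophy, and no rate for hydrocele.

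The reply does not remove the mismatch in limb 1. If perioperative apnoea is intended, the text departs from the intent. Adverse event records are not the endpoint. Stratification by centre does not protect against a judgement of cause that varies with the infant's allocation. The blinded assessors promised under Who will be blinded {17a} cannot restore an episode that the surgeon did not score.

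**Conclusion.** The point holds in a limited form. As worded, an apnoea of 20 seconds or longer that the surgeon attributes to the anaesthetic does not meet the only anaesthesia-type item in the complications outcome. The likely consequences are some lost events, some dilution, and a score that depends on an unblinded judgement of cause. The direction of any resulting bias cannot be told from the document.

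The size is open. Between about 11 and 23 apnoeas per arm would be expected at rates of 6% (assumed) to 12% (the article's upper figure, given in connection with repeated anaesthesia). The share that the wording would exclude is unknown. The conclusion rests on a literal reading of one word in limb 1, and no conduct at any site is alleged. It concerns one component of a secondary outcome, and neither the primary endpoint nor the sample size is touched. It should be corrected before analysis.

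**What to change.** Delete *unexplained* from the apnoea definition. Count any episode that meets the duration criterion or the associated-sign criteria, whatever its presumed cause, after the primary operation and after any re-operation. Keep the existing assessment times. Report apnoea during the hernia-repair admission separately from apnoea reported at the 4-week call, so that the perioperative count can be read on its own without dropping the later reports.

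The cost is a late change to a secondary outcome definition in an open-label trial: Recruitment {15} gives 302 infants included by August 2021. The change should therefore be documented and made before analysis, by people who have not seen results by arm. Re-scoring from the interventions already entered is not enough, because an episode judged explained may never have been entered as apnoea. Adverse event records or charts need to be checked for such episodes, blind to allocation. The change concerns outcome scoring only and leaves patient care as it is.
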